**5.5 Procedures**

Pre-randomisation measurements

To ensure the inclusion and exclusion criteria are met, a 24h urine collection for calcium and blood tests for 25OHD, calcium, albumin and renal function must have been done in the last month. A 75g 2h OGTT result no more than 3 months old must also be available.

Measurements at baseline and at the end of the study

*Anthropometrical and blood pressure assessments**

- Height (to the nearest 0.5 cm), using a wall-mounted stadiometer;
- Body weight (to the nearest 0.1 kg), measured without shoes and in light clothing, using an electronic calibrated scale;
- Waist circumference (to the nearest 0.5 cm), using a tape placed at the midpoint between the lower rib and the upper iliac crest;
- Blood pressure, taken 3 times in the sitting position with an adequate pressure cuff, after a 5-minute rest. The mean of the 3 results will be used for statistical purposes.

*These parameters will also be measured at 2 months

*Body composition*

Fat mass will be measured using dual-energy X-ray absorptiometry (Hologic, Discovery W, Bedford, MA, USA) only at the beginning of the study to correlate fat mass with the dose of vitamin D_3_ needed to reach optimal 25OHD levels.

*Biochemical assessments*

- Fasting blood will be drawn for 25OHD, total calcium, albumin, phosphate, PTH, alkaline phosphatase, osteocalcin, complete lipid profile, HbA_1_C, FFAs, adiponectin, high-sensitive C-reactive protein (hs-CRP) and fibrinogen;
- 2h OGTT after 75g of glucose: glucose, insulin and C-peptide levels will be measured at times -30, -20, -10, 0, 10, 20, 30, 60, 90 and 120 minutes;
- 24h urinary calcium and creatinine;
- Extra aliquot for storage for measurement of other bone markers and markers of inflammation (IL-6 and TNF-alpha) and diabetes when the funds will be available.

*Questionnaires*

- Medical history;
- Food questionnaire to estimate vitamin D and calcium intake [56];
- Physical activity questionnaire [57];
- Questionnaire to estimate sunlight exposure.

*Assessment of β-cell insulin secretion, insulin resistance and beta-cell function*

- **Insulin secretion rate** will be estimated by two methods:
  - The insulinogenic index ([Ins_t30_ – Ins_t0_] ÷ [Glucose_t30_ – Glucose_t0_]), which mainly reflects the first phase of insulin secretion;
  - The deconvolution analysis of C-peptide levels after a glucose load. C-peptide is probably a better indicator of insulin secretion than insulin itself since the latter is subject to hepatic clearance. Pre-hepatic ISR will be calculated from deconvolution of peripheral plasma C-peptide levels using a two compartment mathematical model with standard parameters for C-peptide distribution and metabolism, as previously described using the Chronobiological Series Analyses software (iBridge Network, [www.iBridgeNetwork.org](http://www.iBridgeNetwork.org), University of Chicago) [58]. Use of standard parameters for C-peptide clearance and distribution has been shown to result in insulin secretion rates that differ in each subject by only 10-12% from those obtained with individual parameters and there is no systematic over- or underestimation of insulin secretion. Incremental ISR from baseline during the first 30 minutes divided by incremental glucose and absolute total area under the curve of C-peptide by deconvolution analysis will be compared between baseline and 6 months of treatment.
- **Insulin resistance** will also be assessed by two methods:
  - The homeostasis model assessment for insulin resistance (HOMA-IR) is particularly suitable for obese and/or glucose intolerant subjects and has been shown to highly correlate with measures of insulin sensitivity obtained from the gold-standard procedure (euglycemic clamp technique) [59-61]. It is calculated from fasting insulin and glucose levels as follows: [Fasting insulin (mU/L) X fasting glucose (mmol/L)] ÷ 22.5.
  - Insulin resistance will also be estimated with the revised Quicki index: 1/[log (fasting glucose in mg/dl) + log (fasting insulin in μunits/ml) + log (fasting FFA). This index was shown to better correlate with euglycemic clamp than HOMA-IR in impaired glucose tolerant individuals (r=0,802) [62].
- **Beta-cell function** will be estimated by calculating the disposition index (DI): DI = insulin sensitivity (HOMA-IR) X ISR (deconvolution analysis of C-peptides).

*Evaluation of compliance*

Pill count will be performed after two months and at the end of the study to verify compliance to medication. Participants will be asked to report any change in their medication since the last visit.

*Monitoring of side effects and Safety Issues*

Vitamin D replacement therapy is very safe. Cholecalciferol doses up to 10 000 IU daily have not caused hypercalcemia *per se* in clinical trials [63]. Screening laboratory tests will ensure that subjects with hypercalcemia are not included in the study. Furthermore, at two and 6 months, monitoring of serum 25OHD and calcium levels will be done. Participants will also be instructed about the symptoms of hypercalcemia and asked to contact the research team immediately if these symptoms develop during the course of the study.

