**1. Introduction**

**1.1 Obesity and Diabetes: Magnitude of the problem**

The results of the last national survey, the Australian Diabetes, obesity and lifestyle study (AusDiab), highlighted the rapid and dramatic rise in the prevalence of diabetes and other categories of abnormal glucose tolerance in Australia [1]. Indeed, almost one in four adult Australians had abnormal glucose tolerance in 2000, one of the highest prevalences reported in a developed nation. This epidemic of diabetes is explained, for the most part, by the coincident doubling in the prevalence of obesity over the last 20 years [2].

Accumulating evidence also suggests that vitamin D and calcium play a physiological role in the modulation of systemic inflammation [3-5], renin-angiotensin system [6], pancreatic β-cell function [7-9] and insulin action [10-14]. It could then be expected that a deregulation of these systems leads to type 2 diabetes, hypertension, metabolic syndrome, and cardiovascular disease (CVD).

**1.2 Observational Studies that Support the link between Vitamin D and Calcium Deficiency and type 2 Diabetes, Metabolic Syndrome and CVD**

Seasonal variation in the incidence of type 2 diabetes [15] and deterioration of glycemic control reported at the end of the winter [16], when vitamin D stores reach their nadir, first pointed toward a possible link between vitamin D deficiency and impaired glucose metabolism. Studies reporting higher prevalence rates of vitamin D deficiency in type 2 diabetics compared to normal controls further supported this hypothesis [5, 17]. It is worth noting that this difference persisted even after adjustment for body-mass index (BMI), which had been shown to independently predict low serum levels of 25-hydroxyvitamin D (25OHD), a reliable marker of vitamin D status [18, 19].

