**3.2 Secondary Aims**

- Secondary objectives are to assess, in this population of vitamin D deficient individuals at high risk of type 2 diabetes, the effect of treatment on:
  1. Inflammatory markers;
  2. Adiponectin and osteocalcin;
  3. Insulin resistance using the revised Quicki index;
  4. Blood pressure;
  5. Lipid profile;
  6. Fasting free-fatty acid (FFA) levels;
  7. Body weight.
- We also seek to determine whether vitamin D requirements (to achieve a level of 25OHD ≥75 nmol/L) are influenced by fat mass (dual X-ray absorptiometry - DXA) in this population of overweight individuals.

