**5.2 Randomisation and Intervention**

The proposed study is a prospective, double blind, randomised and placebo controlled 6-month clinical trial. Subjects will be randomly assigned to one of two groups, with stratification according to sex, age (< or >50 years of age) and BMI (< or >30). The treatment group will receive vitamin D_3_ (cholecalciferol) 2000 IU plus calcium carbonate (1200 mg elemental Ca daily) and the control group will take placebo pills. Permuted blocks of 4 treatment allocations will be used to ensure that after each 4^th^ allocation there are equal numbers in each treatment arm. After 8 weeks of treatment, if subjects in the treatment group have 25OHD levels less than 75 nmol/L, the dose of cholecalciferol will be increased to 4000 IU daily to reach optimal levels. On the other hand, subjects in the placebo group and those in the treatment group that reached optimal levels of 25OHD will be given extra placebo pills. To ensure blinding is respected, a person external to the study will look at the 8-week 25OHD results and contact patients to add an extra cholecalciferol or placebo pill to their regime, as appropriate.

The dosage of cholecalciferol has been estimated from the study of Barger-Lux and al., a rigorous trial performed in healthy overweight men [52]. They showed that each mcg (40 IU) of vitamin D_3_ increase the 25OHD concentration by 0.70 nmol/L. Based on the mean 25OHD level reported in populations of obese vitamin D deficient subjects (30 nmol/L) [25, 50, 53] and the expected increment described previously, it can be estimated that 2400 IU daily of vitamin D_3_ would be needed to increase the mean 25OHD level of our population to over 75 nmol/L. Of note, the dose-response relationship was not affected by body weight or fat mass. However, other data suggest that vitamin D requirements might be higher in obese compared to normal weight subjects [54]. Therefore, given that participants in our study will be obese, if adequate 25OHD levels are not reached after 8 weeks, the dose of cholecalciferol will be increased to 4000 IU daily. This dose, given daily for 3 months to 28 healthy adults, increased mean 25OHD levels from 37.9 ± 13.4 nmol/L to 96.4 ± 14.6 nmol/L [55]. None of the subjects had 25OHD levels <75 nmol/L at the end of the study.

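### The fat-mass aim is tied to a dose that the trial observes at only two levels, which discards information and mixes response with baseline 25OHD

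*Protocol*

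**What the plan says.** Protocol section 3.2 sets the aim: "We also seek to determine whether vitamin D requirements (to achieve a level of 25OHD ≥75 nmol/L) are influenced by fat mass". Under body composition, section 5.5 says DXA is done "only at the beginning of the study to correlate fat mass with the dose of vitamin" D3 needed to reach optimal 25OHD. That is the only purpose it gives for the scan.

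Section 5.2 fixes the doses. The active arm starts on "cholecalciferol) 2000 IU plus calcium carbonate (1200 mg elemental Ca daily) and the control group will take placebo pills". After 8 weeks, "if subjects in the treatment group have 25OHD levels less than 75 nmol/L, the dose of cholecalciferol will be increased to 4000 IU daily". No further step is described. The same section assumes that each microgram (40 IU) will "increase the 25OHD concentration by 0.70 nmol/L" and takes a mean starting level of 30 nmol/L.

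Section 5.3 admits any baseline up to 50 nmol/L. Section 1.2 says of BMI: "which had been shown to independently predict low serum levels of 25-hydroxyvitamin D". Section 5.6 has no line for the fat-mass aim. It plans multiple linear regression for predictors of treatment response, without naming fat mass.

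**The concern.** With two dose levels and one decision point, the dose a patient is seen to need is a yes/no record of whether week-8 25OHD was below 75. Three things follow.

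- A continuous measurement is reduced to one bit, and most patients are expected on the same side of the cut.
- Whether a patient crosses 75 depends on the starting level as well as on the rise. The protocol itself links adiposity to low 25OHD, so a correlation with dose can come from baseline alone, from response alone, or from both.
- For a patient still below 75 on 4000 IU, the requirement is known only to exceed 4000 IU.

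At stake is a stated secondary aim. Section 5.2 treats it as open: it cites one study in which fat mass did not affect the dose-response and other data suggesting higher requirements in obesity. The primary comparison, sample size and safety monitoring are not affected.

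**Working it through.** **The plan's own figures.** The protocol gives no power for this aim. Its HOMA-IR calculation reproduces: difference 0.15, SD 0.18 and 90% power give 31.3 by the t test, so 32 per group, and 64/0.8 = 80. The active arm is therefore 40 randomised and about 32 completing.

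**What decides the dose (inputs from 5.2 and 5.3).** Increment = IU/40 × 0.70.
- 2000 IU: 50 × 0.70 = 35 nmol/L, so 75 is reached from a baseline of at least 75 - 35 = 40.
- 4000 IU: 100 × 0.70 = 70 nmol/L, so 75 is reached from a baseline of at least 75 - 70 = 5.

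With one common slope, baseline alone sets the dose: 40-50 gives 2000 IU and 5 to below 40 gives 4000 IU, whatever the fat mass. From the assumed mean of 30, week 8 averages 30 + 35 = 65.

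**Assumptions not in the protocol.** Baseline SD is 10 and increment SD is 12 nmol/L. All correlations are assumed.

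**Hand approximation, n = 32.**
1. With no other links, week-8 SD = √(10² + 12²) = 15.62. The cut is at z = (75 - 65)/15.62 = 0.64, so p = 0.74 go to 4000 IU.
2. Cutting a normal variable there multiplies a correlation by φ(z)/√(p(1-p)) = 0.325/0.439 = 0.74.
3. Power ≈ Φ(atanh|r| × √29 - 1.96).

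*Fat mass related to the increment only (-0.4).*
- Week-8 change: atanh(0.4) × 5.385 = 2.28, power 63%.
- Week-8 level: r = -0.4 × 12/15.62 = -0.307, power 40%.
- Two-level dose: r = -0.307 × 0.74 = -0.227, power 24%.

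*Baseline link of -0.3 added.*
- Week-8 variance = 244 + 2(3 × 4.8) = 272.8, SD 16.52.
- Week-8 level: r = -(3 + 4.8)/16.52 = -0.472, power 79%.
- Two-level dose (factor 0.745): r = -0.352, power 51%.

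*Baseline link only (-0.3; -0.5).*
- Week-8 level: r = -0.192; -0.320, significant in 18%; 43%.
- Two-level dose: r = -0.142; -0.237, significant in 12%; 25%.
- Week-8 change: stays at 5%.

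**Simulation under the same assumptions.**

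| Fat mass related to | Two-level dose | Week-8 change | Week-8 level |
|---|---|---|---|
| increment -0.4 | about 25% | 60-64% | not tabulated |
| increment -0.4 and baseline -0.3 | about 49% | 58-64% | about 78% |
| baseline only, -0.3 to -0.5 | 11-26% | about 5% | not tabulated |

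The last row's 11-26% becomes 11-19% if baseline is limited to 5-50 nmol/L. About 17% of active patients stay below 75 if their increment doubles on 4000 IU.

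**Sensitivity.** With baseline SD 8-12 and increment SD 8-16, the two-level dose has 17-32% power against 63-65% for the change in the increment-only case. A separate simulation used between-patient variation in slope (SD 0.2 nmol/L per microgram), assay SD 5 and n of 32-40. It gave 17-31% against 63-77%, and 11-33% significant results when only baseline was linked.

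**The case against.** The strongest reply is that section 3.2 asks about requirements to reach 75, not about response. A patient who starts lower needs more, so if fatter patients start lower their requirement is truly higher. This stands. A reader might infer that the 11-26% are false positives, but for the stated aim they may be detections of a real difference. What they cannot do is separate that from a difference in response, which is the question section 5.2 leaves open. An analysis that only adjusted for baseline would remove part of what section 3.2 asks.

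Second, section 5.2 also speaks of a needed dose when it interpolates 2400 IU, which is neither trial dose. A requirement interpolated for each patient would be continuous and defined for everyone. With both links present it had 69% power in one re-run, against 62% for the change. The wording does not exclude this, but no per-patient formula is given, and two observed doses is the natural reading.

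Third, the power gap is widest when fat mass is unrelated to baseline, whereas the protocol suggests that it is related. With a link of -0.3, most of the gap to the week-8 change closes. The gap to the continuous week-8 level does not.

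Fourth, a reader might call the variable undefined for patients who never reach 75. They are right-censored and could be ranked as a third category. The cited 4000 IU study had nobody below 75, so the protocol expected few. The 17% depends on the assumed SDs.

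Finally, a SAP could specify a better analysis. Section 5.5 nevertheless names the variable, and that choice is the point here.

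**Conclusion.** The point holds for the variable named in section 5.5, read as the observed dose. It is a dichotomised, partly censored week-8 25OHD that loses power and does not separate response from baseline. At n = 32, with assumed SDs of 10 and 12, power is about 25% against 60-64% for the change when fat mass affects response only. When it is also linked to baseline, power is about 49% against about 78% for the continuous level. The exact figures rest on SDs and correlations that the protocol does not give. The loss from dichotomising does not depend on them.

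A reader might go further and conclude that the trial cannot answer its aim. The documents do not support that. The planned variable keeps some power, the interpolated reading is open, and the data for a good analysis are already scheduled. This is a worthwhile correction to a secondary aim, with no bearing on the primary result.

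**What to change.** In sections 5.5 and 5.6, replace the correlation with dose by a linear regression, in active-arm patients, of continuous week-8 25OHD on baseline DXA fat mass. All of them are assigned 2000 IU until then. Report the slope per kg with its 95% CI twice:
- without baseline 25OHD, for the total effect on reaching 75 (the requirements aim);
- adjusted for baseline 25OHD, for the effect on response. This gives the same fat-mass slope as regressing the week-8 change with the same adjustment.

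Both are needed, because the unadjusted level also carries the baseline link (18-43% significant in the baseline-only case above). Add pill-count compliance and sunlight exposure as a sensitivity adjustment only, given the small n. Report descriptively the proportion on each dose and the proportion still below 75 at 6 months.

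The cost is a few sentences and a little extra analysis. DXA, baseline and 2-month 25OHD, pill counts and the sunlight questionnaire are already scheduled, and dosing does not change.

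### The insulinogenic index uses one of four basal samples, and the protocol does not say which basal samples define fasting values for HOMA-IR

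*Protocol*

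**What the plan says.** All of the following is in section 5.5 of the protocol unless stated otherwise.

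- **Sampling.** For the 2-hour OGTT, glucose, insulin and C-peptide "will be measured at times -30, -20, -10, 0, 10, 20, 30, 60, 90 and 120 minutes". The test is done at baseline and at the end of the study. Four of the ten times (-30, -20, -10 and 0) are basal.
- **Insulinogenic index.** The formula names single time points: "The insulinogenic index ([Ins_t30_ – Ins_t0_] ÷ [Glucose_t30_ – Glucose_t0" (the quote stops just before the closing bracket). The protocol describes it as an index "which mainly reflects the first phase of insulin secretion".
- **HOMA-IR.** "It is calculated from fasting insulin and glucose levels as follows: [Fasting insulin (mU/L) X fasting glucose (mmol/L)] ÷ 22.5". No sampling time is named.
- **Disposition index.** It is built on HOMA-IR: "DI = insulin sensitivity (HOMA-IR) X ISR (deconvolution analysis of C-peptides".
- **Revised Quicki index.** It uses fasting glucose, insulin and free fatty acids, again without a sampling time.
- **Blood pressure.** The same section says that the mean of the three readings will be used. It gives no such rule for the basal OGTT samples.

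Section 3.1 places HOMA-IR, the insulinogenic index and the disposition index under the primary aim. Section 3.2 lists the revised Quicki index as secondary. Section 5.6 bases the sample size on the change in HOMA-IR.

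**The concern.** Replicate basal samples are useful because a single fasting insulin or glucose value carries assay error and short-term fluctuation. The mean of four values with independent errors has one quarter of the error variance of a single value.

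The insulinogenic index formula does not use this. Its time-zero values enter both numerator and denominator, and the error enters the change score twice, at baseline and at 6 months. The values at -30, -20 and -10 minutes are drawn and assayed but do not enter the index.

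For HOMA-IR the question is open. The separate fasting-blood list in section 5.5 contains neither glucose nor insulin, so the fasting values at the two study visits appear to come from the OGTT series. That leaves at least five readings: any one of the four samples, or their mean. If one sample were used, the endpoint behind the sample size would carry avoidable noise, and so would the disposition index.

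**Working it through.** **1. The plan's own figure.** Inputs from section 5.6: difference 0.15, SD 0.18, two-sided alpha 0.05, 32 per group, 20% dropout, unpaired *t* test.

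- Noncentrality = 0.15 / (0.18 × √(2/32)) = 3.33 on 62 degrees of freedom. Power is 90.7%.
- The smallest size reaching 90% is 32 per group by the *t* calculation and 31 by the normal approximation.
- 64 / 0.8 = 80.

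The stated 32 per group and 80 in total reproduce.

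**2. Insulinogenic index, where the text fixes one sample.** The documents give no within-visit variances, so these inputs are assumptions: mean insulin 12 mU/L basal and 75 at 30 minutes; mean glucose 5.8 mmol/L basal and 9.3 at 30 minutes; independent errors; coefficients of variation of 5-25% for insulin (cI) and 2-3% for glucose (cG). With m basal samples averaged, the approximate within-visit variance of the log index is

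cI² × (75² + 12²/m) / 63² + cG² × (9.3² + 5.8²/m) / 3.5²

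| cI | cG | m = 1 | m = 4 | Reduction, formula | Reduction, simulation |
|---|---|---|---|---|---|
| 5% | 2% | 0.00756 | 0.00666 | 11.8% | 12.0% |
| 10% | 2% | 0.01846 | 0.01736 | 5.9% | 5.9% |
| 15% | 3% | 0.04153 | 0.03906 | 5.9% | 6.0% |
| 25% | 3% | 0.09967 | 0.09612 | 3.6% | 4.0% |

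The gain is about 4-12%. It is small because the single 30-minute sample dominates: in the insulin term, 75² = 5625 stands against 12² = 144.

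**3. HOMA-IR, where the text is silent.** Let f be the share of the variance of the change in HOMA-IR that is single-sample basal error, and r the correlation of that error across the four samples. The documents give neither. Assume also that 0.18 is a single-sample SD. Then

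SD with averaging = 0.18 × √(1 − f × (1 − (1 + 3r)/4))

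| f | r | Variance ratio | SD | Power at 32 per group |
|---|---|---|---|---|
| 0 | – | 1 | 0.180 | 90.7% |
| 5% | 0 | 0.963 | 0.177 | 91.7% |
| 5% | 0.5 | 0.981 | 0.178 | 91.2% |
| 20% | 0 | 0.850 | 0.166 | 94.5% |
| 20% | 0.5 | 0.925 | 0.173 | 92.7% |
| 50% | 0 | 0.625 | 0.142 | 98.6% |
| 50% | 0.5 | 0.813 | 0.162 | 95.4% |

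Across this range power moves from 90.7% to between 91.2% and 98.6%.

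**The case against.** The strongest case against has four parts.

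- **HOMA-IR is not fixed on one sample.** A reader might infer that precision is lost on three primary outcomes. The documents do not support that. The HOMA-IR sentence, "It is calculated from fasting insulin and glucose levels as follows", is compatible with a mean of the four samples, and which samples count as fasting is a detail that a SAP may settle. The disposition index inherits HOMA-IR's status. This part stands, and limits the established loss to the insulinogenic index. The blood-pressure rule shows that the authors stated averaging where they intended it, but that is a hint and no proof.
- **The larger figures belong to HOMA-IR.** Power up to 98.6% depends on an assumed f and on 0.18 being a single-sample SD. That SD comes from a cited study whose sampling the protocol does not describe. If that study averaged basal samples, 0.18 already contains the gain. This stands. The HOMA-IR figures are a range under assumptions.
- **The extra basal samples may have another use.** The protocol also compares "Incremental ISR from baseline during the first 30 minutes divided by incremental glucose", and the early samples could supply that baseline, although the text does not say so. This is fair for C-peptide and glucose. It does not explain the insulin assays at -30, -20 and -10 minutes, which have no stated use unless fasting means an average.
- **Nothing is biased.** The same formula applies to both arms and both visits. That is correct: the point concerns efficiency and definition only.

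None of this reaches the insulinogenic index, whose formula the protocol itself writes with time-zero values. A SAP that averaged would depart from it.

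**Conclusion.** The point holds in a limited form. As written, the insulinogenic index leaves out three of the four basal insulin and glucose values at each visit. Using them would cut its within-visit variance by about 4-12% under the assumed means and coefficients of variation. The cut in the variance of the change score would be smaller to the extent that subjects also vary between visits.

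For HOMA-IR, the disposition index and the revised Quicki index the loss is possible but not established, and its size cannot be derived from the documents. The range of about 91-99% power for HOMA-IR holds only if 5-50% of the variance of the change is single-sample error, with correlation 0 to 0.5 across samples, and if 0.18 is a single-sample SD.

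A reader might also infer that the trial is underpowered or the sample size miscalculated. It is not: 32 per group and 80 in total reproduce. This is a nearly free improvement and a clarification, with a benefit that is probably modest.

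**What to change.** In section 5.5, define basal insulin and basal glucose as the mean of the -30, -20, -10 and 0 minute samples, computed the same way at baseline and at 6 months. Use these means:

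- in the insulinogenic index, in place of the time-zero insulin and glucose;
- in HOMA-IR, and through it in the disposition index;
- in the revised Quicki index for glucose and insulin, with free fatty acids kept as the fasting value already listed.

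Keep the time-zero version as a sensitivity analysis, and fix the definition before outcome data are seen.

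The cost is a few lines of text. The samples are already scheduled and assayed, so nothing is added for participants or the laboratory, and the sample size need not change. The one drawback is slightly reduced comparability with reports that use a single fasting sample, which the sensitivity analysis covers.

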**3. Aims/Hypothesis**

**3.1 Primary Aim**

The primary aim of this study is to determine if adequate vitamin D supplementation (2000-4000 IU of vitamin D_3_ daily, assessed by a serum 25OHD level of ≥75 nmol/L) and calcium supplementation (1200 mg daily) in vitamin D deficient individuals at high risk of type 2 diabetes improve:

- Insulin sensitivity (homeostasis model assessment of insulin resistance – HOMA-IR);
- Glucose-stimulated insulin secretion (insulinogenic index and deconvolution analysis of C-peptide levels after a glucose load);
- Beta-cell function (disposition index).

**Primary Hypothesis:** Combined treatment with VD and calcium will significantly improve the insulin sensitivity, glucose-stimulated insulin secretion and β-cell function of VD deficient men and women at high risk of type 2 diabetes compared with placebo.

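### The disposition index is written with HOMA-IR uninverted, so its sensitivity component runs backwards and the beta-cell conclusion can be wrong

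*Protocol*

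**What the plan says.** Protocol section 5.5 places HOMA-IR among the measures of insulin resistance, introduces it as "The homeostasis model assessment for insulin resistance (HOMA-IR" and computes it as "Fasting insulin (mU/L) X fasting glucose (mmol/L)] ÷ 22.5". A few lines further on it defines DI: "DI = insulin sensitivity (HOMA-IR) X ISR (deconvolution analysis of C-peptides".

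Section 3.1 uses the same shorthand in the first item of the primary aim, "Insulin sensitivity (homeostasis model assessment of insulin resistance – HOMA-IR", and makes DI the third item: "Beta-cell function (disposition index". The primary hypothesis is that treatment "will significantly improve the insulin sensitivity, glucose-stimulated insulin secretion and β-cell function of VD deficient men and women".

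Section 5.6 compares the change in DI between arms with an unpaired t test and lets skewed data be log-transformed or analysed non-parametrically. Neither that section nor any other inverts the HOMA-IR term.

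**The concern.** A disposition index is meant to express secretion relative to sensitivity, and the formula does name sensitivity as its first factor. The quantity placed there, however, rises with resistance by the protocol's own definition. The label and the number point in opposite directions.

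What is at stake is one of the three items in the primary aim. A fall in HOMA-IR, which counts as success on the first item, pulls the third item down. Conversely, a participant who becomes more resistant and secretes more insulin to compensate would score as having better beta-cell function.

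This cannot be repaired when the results are read. Only one of the two factors is inverted, so the written index is not a mirror image of the intended one. On the log scale the written form is log ISR + log HOMA-IR and the intended form is log ISR - log HOMA-IR. Changing the sign of the first does not give the second.

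**Working it through.** **Inputs from the protocol.** The HOMA-IR and DI formulas (section 5.5). A difference in delta HOMA-IR of 0.15, SD 0.18, two-sided alpha 0.05, 90% power, 32 per group, 20% dropout and 80 in total (section 5.6).

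**Assumed inputs.** The protocol gives no baseline HOMA-IR, so a range of 1.5 to 5 is used. The 0.15 is taken as a fall. Constant ISR and the 20% changes below are illustrations.

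**1. The plan's own figure.** The normal approximation gives n = 2 x (1.960 + 1.282)^2 x (0.18/0.15)^2 = 30.3, so 31 per group. The exact noncentral t gives 89.8% power at 31 and 90.7% at 32, so 32 per group reproduces. Then 64/0.80 = 80. These figures concern HOMA-IR, not DI, and the point does not touch them.

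**2. Direction of each form.** Let r = HOMA-IR after / before and s = ISR after / before.

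- DI as written changes by the factor r x s.
- DI with the reciprocal changes by the factor s / r.

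When sensitivity improves (r < 1), the written form rises only if s > 1/r, whereas the reciprocal form rises whenever s > r. The two have opposite signs for every s between r and 1/r, a range that includes constant ISR (s = 1).

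**3. The protocol's 0.15, as a fall at constant ISR.** Here r = (baseline - 0.15)/baseline.

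| Assumed baseline HOMA-IR | DI as written | ISR/HOMA-IR | Rise in ISR at which the written DI stops falling |
|---|---|---|---|
| 1.5 | -10.0% | +11.1% | +11.1% |
| 2 | -7.5% | +8.1% | +8.1% |
| 3 | -5.0% | +5.3% | +5.3% |
| 5 | -3.0% | +3.1% | +3.1% |

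**4. Larger illustrative change.** Fasting insulin goes from 15 to 12 mU/L with glucose at 6.0 mmol/L. HOMA-IR is 15 x 6/22.5 = 4.0 before and 12 x 6/22.5 = 3.2 after, so r = 0.8.

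| Change in ISR | DI as written | ISR/HOMA-IR |
|---|---|---|
| -20% | 0.8 x 0.8 = 0.64 (-36%) | 0.8/0.8 = 1.00 (0%) |
| 0 | 0.80 (-20%) | 1.25 (+25%) |
| +10% | 0.88 (-12%) | 1.375 (+37.5%) |
| +25% | 1.00 (0%) | 1.56 (+56%) |
| +40% | 1.12 (+12%) | 1.75 (+75%) |

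**5. Worsening resistance with compensation.** If HOMA-IR and ISR both rise 20%, the written DI is 1.2 x 1.2 = 1.44 (+44%), while ISR/HOMA-IR is 1.2/1.2 = 1.00.

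**The case against.** The formula names sensitivity in words and gives HOMA-IR in brackets as its source, and section 3.1 uses the same shorthand. A missing reciprocal is the likely explanation, and a competent analyst may well supply it. This stands as an account of how the text arose. It does not remove the problem, because the written formula is the only definition of DI in the document and an analyst who follows it computes a different index. An SAP may exist, but a formula that the protocol states wrongly still has to be corrected.

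A reader might infer that DI always moves the wrong way and that the beta-cell conclusion would therefore be wrong. The documents do not support that. ISR enters in the right direction, and the primary hypothesis expects secretion to improve along with sensitivity. With HOMA-IR down 20% and ISR up 40%, the written DI rises 12%, which is the right sign although well short of the +75% from the reciprocal form.

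A reader might also infer that the HOMA-IR and revised Quicki analyses are faulty, since section 3.1 calls HOMA-IR a sensitivity measure and section 5.5 lists Quicki, an index that rises with sensitivity, under resistance. Both formulas are written out, Quicki does not enter DI, and no calculation or test changes with the label. Those are matters of wording.

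The size of the effect does rest on assumed inputs. The 20% changes are not from the protocol, and its own 0.15 gives smaller shifts. Reading an unchanged ISR/HOMA-IR as unchanged beta-cell function also presumes an exact inverse relation that the protocol does not establish.

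**Conclusion.** The formula is wrong as written: a resistance measure stands uninverted where the text calls for sensitivity, and nothing else in the protocol inverts it. The contradiction is visible within section 5.5 and needs no assumption.

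The consequence is conditional. The sensitivity component is reversed and the secretion component is not, so the conclusion on beta-cell function can be wrong, depending on how ISR moves. For a 0.15 fall in HOMA-IR at constant ISR, the written and reciprocal forms have opposite signs at any baseline above 0.15. Over assumed baselines of 5 down to 1.5, the shift is about -3% to -10% against about +3% to +11%. Because DI belongs to the primary aim, this should be corrected before analysis.

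**What to change.** Before unblinding, so that the choice of formula cannot appear to depend on the data, amend section 5.5 as follows:

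- Define DI with a true sensitivity term: DI = ISR x (1/HOMA-IR).
- State which secretion quantity enters as ISR. Section 5.5 derives two from the deconvolution: the 30-minute incremental ISR divided by incremental glucose, and the total area under the curve.
- State that a higher DI means better beta-cell function.
- Log-transform DI only if the chosen ISR quantity is strictly positive. The incremental ratio can be zero or negative, in which case its logarithm is undefined.

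The cost is a few lines of text. Fasting insulin, fasting glucose and C-peptide are already collected, so no samples, visits or participants are added.
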